## Research Question/Hypothesis

An integrated model of HIV care, that includes the WHO PEN, will identify and modify risk factors in more women when compared to a HIV management plan that does not include screening and prevention of atherosclerotic cardiovascular disease.

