**Intervention group**: There are 245 HIV infected women between 18 and 49 years of age, who have been on ART for more than 1 year and attending the CAPRISA Research Clinic in Umlazi. These women were enrolled into the PEPFAR PROMise Ongoing Treatment Evaluation (PROMOTE) observational study from May-June 2017. This study has been implemented to provide long-term follow-up data on safety outcomes of widespread use of combination antiretrovirals (cART) among an already well-characterized cohort of HIV infected mothers and their children who previously enrolled in the multi-site PROMISE study. This cohort was selected for the proposed intervention arm because the principal investigator is based at the research clinic. Women will be briefed at their next PROMOTE study visit and the 1^st^ 200 interested candidates meeting all eligibility criteria will be co-enrolled into the Intervention arm of the Sub-study.

**Control group**: The Tier data base will be used to select HIV infected women aged between 18-49 years, receiving ART for more than 1 year at the Umlazi Gateway PHC. Scheduled clinic visits at similar time points to the anticipated clinic visits in the intervention group will be used to establish a list of potentially eligible women. Following a matched pool of data, the first 200 women fulfilling the inclusion criteria, who attend the clinic for their next appointment and who consent to study participation will be enrolled.

1. Data sources

- Intervention group: Each participant in the intervention group will be assigned a new Participant identifier number (PID) in addition to the PROMOTE PID. History taking and physical exam, as well as laboratory results and where applicable ultrasound reports, will be entered directly into a data collection tool on a Microsoft Excel spreadsheet (Appendix I).
- Control group: Participants will be assigned a PID in addition to their clinic chart number. Information from clinic patient medical records will be entered directly into the data collection tool (Appendix II). At the final study visit; history, physical exam, lab report finding and ultrasound findings (where applicable), will be source documented.

1. Measures to ensure validity

- Internal
- The prospective nature of the study, large sample size, careful matching between cohorts by age category and by duration of ART aims to counteract the potential for selection bias.

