- Information bias in chart review will be controlled by training of staff involved in data collection. Missing information
- Loss to follow up – a retention plan will be place to send clinic appointment reminders by sms or whatsapp, telephone calls in the case of missed visits and occasionally home visits when deemed necessary.
- Laboratory sample measurements will be performed by a certified laboratory.
- External -The larger proposed sample size will allow for external validity / generalizability.

1. List of Variables to be measured and schedule of evaluations

| CVD risk factors | Intervention Arm  (at main study PROMOTE scheduled visits)  Year 1(0+6m), Year 2(12+18m), Year 3(24+30m), Final study Visit (36m) | Control Arm | |
| --- | --- | --- | --- |
|  |  | **Year 1, 2, 3 (not including end of study visit) | Year 3 (end of study-36months) |
| Non-modifiable | Age (Categories in 5 year) | Age (Categories in 5 year) | Age (Categories in 5 year) |
|  | Race (A, I, W, C, O) | Race (A, I, W, C, O) | Race (A, I, W, C, O) |
|  | Family history of CVD in first degree relatives |  | Family history of CVD in first degree relatives |
| Modifiable | Smoking (Current, Never, Past) |  | Smoking (Current, Never, Past) |
|  | Unhealthy Diet |  | Unhealthy Diet |
|  | Exercise (minutes per week) |  | Exercise (minutes per week) |
|  | ART duration in years | ART duration in years | ART duration in years |
|  | ARV regimen | ARV regimen | ARV regimen |
|  | Viral load | Viral load | Viral load |
|  | CD4 count | CD4 count | CD4 count |
|  | BMI (6monthly) | BMI (6monthly) | BMI |
|  | Waist Circumference (6 monthly) |  | Waist Circumference |
|  | Systolic BP (6monthly) | Systolic BP | Systolic BP |
|  | Pulse (6monthly) |  | Pulse |
|  | Fasting Glucose (annual) |  | Fasting Glucose |
|  | Fasting Lipogram (annual) | Fasting Lipogram | Fasting Lipogram |
|  | hsCRP (annual) |  | hsCRP |
|  | Urine Microalbumin (annual) |  | Urine Microalbumin |
|  | *Carotid intima media thickness |  | Carotid intima media thickness |
|  | CVD risk % by Framingham |  | CVD risk % by Framingham |
|  | CVD risk % by DAD |  | CVD risk % by DAD |
|  | CVD risk % by WHO/ISH |  | CVD risk % by WHO/ISH |

*Only at year 3 in women aged over 40 years **Data collection through chart review

1. Plan for Data collection

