- **Intervention group**: The prevalence of CVD risk factors will be determined by data collection through history taking, physical examination, and laboratory and radiology investigations as per the data collection tool. CVD risk assessment will be performed annually using a combination of the WHO and International Society of Hypertension cardiovascular risk prediction (WHO/ISH) and the DAD CHD equation. The intervention proposed is a modified WHO PEN algorithm incorporated into HIV management guidelines at study entry. Trends in all risk factors will be monitored, and new risk factors identified, with 6 monthly intervention during the first year, and annually for three years thereafter.
- **Control group**: Following informed consent, data will be collected from the participants ARV clinic medical chart as per the data collection tool. Standard of care HIV management and primary health care will be provided by public sector clinic staff according to current national guidelines. No study investigations or study questionnaires will be carried out at entry visit until the final study visit. There will be regular telephonic follow up with the participants to maintain study retention. Chart review data collection at 6 monthly intervals. CVD risk factors, as per outcomes described above, will be measured by the study at a single 3 year final study visit. Information obtained will be conveyed to the clinic staff for further management if required.

1. Plan for Data handling/processing

- Data will be analysed using SAS or SPSS software

1. Statistical methods

- Descriptive statistics-continuous variables will be represented by means, medians, prevalence, standard deviation.

The categorical variables will be represented by N+%

- Analytic statistics

The continuous variables will be compared by use of t-tests or Wilcoxon rank sum tests.

The categorical variables will be compared using Chi sq or Fisher’s exact test/

- Logistic regression will be applied to identify predictors of cardiovascular disease between the two arms, and between those participants who exhibit atherosclerosis by carotid intima thickness and those who don’t.

1. List of possible confounders

- Women in the intervention group are already enrolled in a study with controlled settings. These women may have commenced ART with a higher baseline CD4 counts.
- Multivariate logression analyses will be utilized in order to control for confounders.

1. List of associations to be measured

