# Ethical Considerations

- Permissions needed to conduct the study will be obtained from the University of KwaZulu- Natal Biomedical Research Ethics Committee, Prince Mshiyeni Memorial Hospital, KwaZulu-Natal Department of Health and the PROMOTE protocol team.
- Written informed consent form will be obtained prior to any study procedure.
- All study procedures will be conducted in a manner to protect participant privacy and confidentiality.
- There will be no additional reimbursement in the intervention arm of the proposed sub study. Participants enrolled in the PROMOTE study are reimbursed using PROMOTE funds. There will be no reimbursement in the control arm with the exception of the final study visit, during which additional lab assessments will be carried out during their routine PHC visit. .

#

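### In controls only, BMI and systolic BP switch from clinic-chart readings to study measurement at month 36 with no overlapping reading, so control-arm change may include a method offset

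*Protocol*

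**What the plan says.** All the relevant text is in the Protocol, mostly under Overview in the research design and methods chapter.

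- **Control arm before month 36.** Under data sources, "Information from clinic patient medical records will be entered directly into the data collection tool (Appendix II". The schedule of evaluations splits the control arm into two columns, headed "Year 1, 2, 3 (not including end of study visit) | Year 3 (end of study-36months". Only the first carries the footnote "Data collection through chart review". The data collection plan adds that charts are reviewed every 6 months and that the study carries out no investigations in controls until the final visit.
- **Control arm at month 36.** "CVD risk factors, as per outcomes described above, will be measured by the study at a single 3 year final study visit". Ethical Considerations describes this as the visit "during which additional lab assessments will be carried out during their routine PHC visit".
- **Intervention arm.** History, examination and laboratory data are collected at research visits at months 0, 6, 12, 18, 24, 30 and 36.
- **The two variables.** The schedule rows (intervention, control chart, control month 36) read "BMI (6monthly) | BMI (6monthly) | BMI" and "Systolic BP (6monthly) | Systolic BP | Systolic BP". Waist circumference and pulse have no control value before month 36.
- **Purpose.** The hypothesis is that integrated care "will identify and modify risk factors in more women when compared to a HIV management plan" without such screening. The first primary objective likewise covers both identifying and modifying risk factors.
- **Safeguard.** For chart data, the validity section names only training of the staff who collect the data.

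**The concern.** Modification of a risk factor is a statement about change. The arms are formed by convenience sampling from two different clinics, and the list of confounders anticipates that they may differ at entry. A month-36 comparison alone therefore cannot separate an effect of the programme from a difference that was already there, and the entry values carry real weight. Among the examination measures, only BMI and systolic BP have earlier values in both arms.

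For these two, the source changes in one arm only, and at the final time point. If routine clinic readings and study readings differ systematically (device, cuff, rest period, scale, staff), that difference is added to the control arm's change. In the intervention arm a constant method cancels. The offset would be confounded with both arm and time, and depending on its sign it could create or hide an apparent effect. Training abstractors protects against copying errors; it does not affect how the clinic took the reading. If no chart value is collected at month 36, later analysis wording cannot supply it.

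**Working it through.** **1. Source of each reading, from the schedule and the data collection plan**

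| | Months 0 to 30 | Month 36 |
|---|---|---|
| Intervention BMI, systolic BP | study | study |
| Control BMI, systolic BP | clinic chart | study |

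Study-measured time points are 7 of 7 in the intervention arm and 1 of 7 in controls. Month 30 as the last chart point is inferred from the 6-monthly chart review; the schedule prints the 6-monthly label for control BMI but not for control systolic BP. The fasting lipogram also appears in both control columns, so the same switch may apply to it.

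**2. Where the offset enters.** Let *d* be the study-minus-chart difference in controls.

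- Control change, entry to month 36 = true change + *d*.
- Intervention change = true change.
- Difference in change (intervention minus control) = true difference − *d*.
- Difference at month 36 alone: both arms are study-measured, so *d* does not appear. The same holds for the share of women above a cut-off at month 36.

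**3. Illustration for systolic BP.** The documents give neither an SD of change nor an offset. Assumptions: 200 per arm (the planned size), no true effect, two-sided 5% test, SD of change 15 mmHg (20 as an alternative).

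SE = SD × √(2/200) = 1.50 mmHg for SD 15 and 2.00 for SD 20.

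Probability of a significant result = Φ(−1.96 + d/SE) + Φ(−1.96 − d/SE).

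| Offset *d* (mmHg) | SD 15 | SD 20 |
|---|---|---|
| 1 | 10% | 8% |
| 2 | 27% | 17% |
| 3 | 52% | 32% |
| 5 | 92% | 71% |

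With 180 per arm (10% loss) and SD 15, SE = 1.58, and offsets of 3 and 5 mmHg give about 48% and 88%.

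**4. With adjustment for the entry value.** The offset then sits in the control baseline and is multiplied by the regression slope. Assume a within-woman correlation of 0.5 and equal variances. An SD of change of 15 then implies an SD of 15 at each time, because √(2 × 15² × (1 − 0.5)) = 15, and a slope of 0.5. Residual SD = 15 × √(1 − 0.25) = 12.99.

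- 180 per arm: SE = 12.99 × √(2/180) = 1.37. An offset of 3 mmHg leaves a bias of 1.5 mmHg and about 20% rejection; 5 mmHg leaves 2.5 mmHg and about 45%.
- 200 per arm: SE = 1.30, giving about 21% and 49%.

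Adjustment roughly halves the bias here. A slope nearer 1 would shrink it less.

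**5. BMI.** With an assumed SD of change of 2.5 kg/m² and 200 per arm, SE = 0.25. Unadjusted, offsets of 0.2, 0.3, 0.5 and 1.0 kg/m² give about 13%, 22%, 52% and 98%.

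**The case against.** The strongest reply is that the protocol never proposes the affected analysis. It names t-tests or Wilcoxon tests, chi-square or Fisher tests and regression, and defines no change endpoint; that definition may stand in an analysis plan that is not shown. The risk-score comparison uses controls at year 3 only. Metabolic syndrome, the sample-size outcome, needs waist and glucose, which controls have only at month 36. This stands: the problem is conditional on a comparison of change. But the hypothesis and first objective call for one, and the missing chart reading is a data-collection matter that no analysis plan can repair afterwards.

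Two stronger readings are tempting, and neither is supported. A reader might infer that the protocol runs the two control sources together as one series. It does not: the schedule puts them in separate columns and footnotes only the first as chart review. A reader might also infer that the switch distorts the shares of women above a blood-pressure or obesity cut-off at month 36. It does not, because both arms are study-measured then; only apparent transitions within controls would be affected.

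It is also fair that no document says the device, scale or staff actually differ, that small offsets do little harm, and that baseline adjustment reduces the bias. All of this limits the size of the concern; none of it provides a way to check the offset.

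**Conclusion.** The point holds in a limited form. Control BMI and systolic BP change source at month 36, the intervention arm's do not, and no overlapping reading is planned. An entry-to-month-36 change in controls would include any method offset. Its existence is plausible but undocumented, and its size and sign are unknown. The rejection rates are illustrations under assumed SDs, offsets and correlation. For systolic BP with 200 per arm and SD 15 mmHg they run unadjusted from about 10% (1 mmHg) to 92% (5 mmHg), and are lower with baseline adjustment. They are not estimates of this trial's error rate. The month-36 between-arm comparison stands as planned. This is a cheap improvement worth making, not a defect that invalidates the design.

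**What to change.** 1. Extend control chart abstraction to month 36: record the routine clinic BMI and systolic BP from that visit, or the nearest chart reading if none was taken. The final study assessment already coincides with a routine clinic visit.
2. Base change on like with like: chart entry to chart month 36 in controls, study entry to study month 36 in the intervention arm.
3. Keep the study-measured control values for the month-36 between-arm comparison.
4. Report the paired study-minus-chart difference in controls at month 36, and use it as a sensitivity check on the earlier chart values. State that this assumes a constant offset over three years, across whichever staff and equipment took the earlier readings; the documents cannot confirm that.

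**Cost.** Two more fields from charts already reviewed every 6 months, plus a few lines of protocol or analysis-plan text. No extra participants and no new procedure. Routine readings are noisier, so the control change estimate will be somewhat less precise.

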# research design and methods

## Overview

1. Study Setting: Umlazi/Philasande Research Clinic and Gateway Umlazi Clinic
2. Study Design: This study is a prospective two-arm, quasi-experimental design comparing a primary health care intervention plan with usual care.
3. Target Population: HIV infected women attending PHC
4. Study population: HIV infected women aged from 18 to 49 years of age and receiving HIV care at PHC clinics.
5. Inclusion criteria

- HIV infected women
- On ART for at least 1 year
- Equal to/older than 18 years of age
- Equal to/younger than 49 years of age
- Plans to remain in the study catchment area for at least 3 years

1. Exclusion criteria

- Participant declines study participation

1. Sampling

• Size of sample

400 HIV-infected women consisting of an intervention arm of 200 women co-enrolled in the PROMOTE study at the Umlazi CRS (see method of sampling for details), and a control arm of 200 women receiving HIV care at the PHC. With a 20-30% estimated prevalence of metabolic syndrome in people living with HIV without any specific intervention in the risk factor modification of cardiovascular disease and a proposed 10-15% estimated incidence of metabolic syndrome in the intervention arm, 132 participants per arm would allow for 80% power. An additional 10% can be added to allow for loss to follow-up. The larger proposed sample size will allow for external validity / generalizability.

- Method of selecting sample

Two HIV-infected female cohorts will be matched for receipt of ART duration >1 year and for age will be compared in the study. Method of selection will be via convenience sampling.

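### In a non-randomised comparison, the protocol names unadjusted two-sample tests and gives continuous risk factors and risk scores no clearly stated arm comparison adjusted for the matching factors, whose balance among the women analysed is not guaranteed

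*Protocol*

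**What the plan says.** All of this is under Research design and methods, Overview.

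- **Design.** "This study is a prospective two-arm, quasi-experimental design comparing a primary health care intervention plan with usual care". Sampling is by convenience.
- **Matching.** The sampling item says: "Two HIV-infected female cohorts will be matched for receipt of ART duration >1 year and for age will be compared in the study". The internal-validity item puts it differently: "careful matching between cohorts by age category and by duration of ART aims to counteract the potential for selection bias".
- **Enrolment.** From 245 women in the parent study, the first "200 interested candidates meeting all eligibility criteria will be co-enrolled into the Intervention arm of the Sub-study". For controls: "Following a matched pool of data, the first 200 women fulfilling the inclusion criteria, who attend the clinic for their next appointment and who consent". No pairs, strata or age quotas are described.
- **Tests.** "The continuous variables will be compared by use of t-tests or Wilcoxon rank sum tests" and "The categorical variables will be compared using Chi sq or Fisher’s exact test".
- **Models.** Logistic regression is planned for predictors of cardiovascular disease between the arms and by carotid atherosclerosis status. Under possible confounders: "Multivariate logression analyses will be utilized in order to control for confounders". The confounders named there are enrolment in a controlled study and higher CD4 at ART start.
- **Variables.** Age (in 5-year categories), ART duration and CD4 are listed for both arms throughout. Waist, fasting glucose, hsCRP and the three risk scores are listed for controls only at month 36.

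**The concern.** In a non-randomised study the factors used to make the arms comparable should also appear in the comparison of the arms. Here the tests named treat the arms as two unrelated samples.

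Age matters by the protocol's own account. It is an input to the WHO/ISH score (literature review, CVD risk assessment tools in HIV), and the table of associations sets age and ART duration against every listed risk factor. Controls have no study measurement of waist, glucose, hsCRP or risk score at entry, so a change-from-baseline analysis cannot absorb initial differences in these outcomes. Age and ART duration are among the few covariates available in both arms from the start.

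Two different things are at stake, under opposite conditions:

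- If the women analysed differ in age, the unadjusted difference mixes the intervention with age.
- If they are balanced, the unadjusted estimate is not biased by age, but variation due to age and ART duration stays in the error term and precision is lost.

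**Working it through.** **1. The plan's own figure.** The protocol gives 132 per arm for 80% power on metabolic syndrome (20-30% versus 10-15%). Alpha is not stated; two-sided 0.05 is assumed. For 30% versus 15%, mean proportion 0.225:

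n = [1.96·√(2·0.225·0.775) + 0.842·√(0.30·0.70 + 0.15·0.85)]² / 0.15² = 120.5, so 121 per arm; with continuity correction, 134.

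The second is close to 132. It is the size for an unadjusted comparison of two proportions. The figure is not in dispute.

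**2. Does the plan secure the match?**

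- In the sampling item, the ART match is a duration above 1 year. The inclusion criteria already require at least 1 year on ART, so this version balances almost nothing. The validity item claims matching on duration itself.
- The match is applied to a list of records. The women enrolled are those who come first and consent, and the outcomes come from those seen at month 36.
- Balance is therefore encouraged by the matched pool but not fixed by quota, stratum or pairing.

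**3. Bias if an age gap remains (continuous outcome, no true effect).** The documents give no age-outcome correlation ρ, age SD or age gap. Assumed: ρ 0.3 or 0.5, SD 6-8 years, gap 2 years, and n = 200 per arm or 180 after 10% loss. The noncentrality is

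λ = ρ·(gap/SD) / √(2/n), and the false-positive rate is P(Z > 1.96 − λ) + P(Z < −1.96 − λ).

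| ρ | SD | n per arm | λ | False-positive rate |
|---|---|---|---|---|
| 0.3 | 8 | 180 | 0.71 | 11.0% |
| 0.3 | 6 | 200 | 1.00 | 17.0% |
| 0.5 | 8 | 180 | 1.19 | 22.0% |
| 0.5 | 6 | 200 | 1.67 | 38.5% |

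**4. The same for binary metabolic syndrome.** Assumed: 200 per arm, age SD 6, odds ratio 1.2-1.5 per 5 years of age, control rate 20-30%. An age gap of 1-3 years gives a spurious difference of 0.6-4.7 percentage points and a false-positive rate of about 5-17%. For comparison, the pair that nearly reproduces 132 implies a 15-point difference.

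**5. Precision if balance holds (continuous outcome).** Adjustment multiplies the residual variance by 1 − ρ². Where the usual formula gives 80% power (noncentrality 2.80), adjusted power is Φ(2.80/√(1 − ρ²) − 1.96). With exact age balance the unadjusted test is conservative, and its actual power is Φ(0.842/√(1 − ρ²)), slightly above 80%.

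| ρ | Unadjusted, actual | Adjusted | Gain (points) |
|---|---|---|---|
| 0.3 | 81.1% | 83.6% | 2.5 |
| 0.4 | 82.1% | 86.4% | 4.3 |
| 0.5 | 83.4% | 89.9% | 6.5 |

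**6. Precision for metabolic syndrome.** Simulation with 132 per arm, identical age distributions, and a Mantel-Haenszel test without and with six age bands; the log-odds slope per SD of age is assumed.

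| Rates | Slope | Unstratified | Stratified |
|---|---|---|---|
| 30% v 15% | 0.5 | 84.0% | 84.6% |
| 30% v 15% | 1.0 | 85.8% | 89.0% |
| 20% v 10% | 0.5 | 63.4% | 64.7% |
| 20% v 10% | 1.0 | 64.7% | 68.3% |

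The gain is 0.6 to 3.6 points, roughly 1 to 4.

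**The case against.** **Adjustment is already planned.** This stands in part. The protocol does say that confounders will be controlled by multivariable analysis. The garbled word in that sentence may mean regression in general, which would reach continuous outcomes. The confounder list is headed as possible confounders and is not said to be complete, and a full covariate list could properly sit in an SAP that is not shown. A reader might infer that the analysis ignores age and ART duration altogether; the text does not support that. What remains is that the protocol itself names the two-sample tests, names only logistic regression clearly, and does not say which result is the main arm comparison.

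**The tests are not expressly tied to the arms.** True. The efavirenz versus lopinavir/r objective would also use them. In a two-arm study, comparing the arms is still the natural reading, and no other method is stated for continuous outcomes.

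**Controls come from a matched pool.** This stands. A reader might infer that first-come enrolment breaks the match. The documents do not show that: it would require attendance, consent or dropout to be related to age, and a retention plan is in place. The match is unsecured, not shown to be lost.

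**The sizes are assumed, and small for the powered outcome.** This also stands. The 22-39% false-positive rates need ρ = 0.5. For metabolic syndrome, the only outcome used in the sample-size statement, the power gain is modest and logistic regression already applies.

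**Conclusion.** The point holds in a limited form. As written, the plan leaves continuous risk factors and risk scores without a clearly stated adjusted arm comparison. It does not connect its confounder control to the factors it matched on, and it does not secure their balance among the women analysed.

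Bias and lost precision are alternatives and should not be added together. Neither size can be derived from the documents. Under the stated assumptions, a 2-year age gap raises the false-positive rate for a continuous outcome to about 11-17% at ρ = 0.3. With balance intact, using age gains about 1-4 points of power for metabolic syndrome. The direction of any bias is unknown.

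This is more than a missing covariate list, because the named tests do not fit the matched, non-randomised design. It is worth correcting because the remedy is cheap.

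**What to change.** In Statistical methods, make the main between-arm comparison of each risk factor and risk score a regression: linear for continuous outcomes (log-transformed where skewed, such as hsCRP) and logistic for binary ones. Covariates:

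- arm;
- age at entry: the 5-year category listed in the variables table, or years if recorded;
- ART duration at entry;
- CD4, the measurable confounder the protocol already names: the value at ART start if the records hold it, otherwise the value at entry, so that it precedes the intervention.

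Report the adjusted difference or odds ratio with a 95% CI. Keep the t-test, Wilcoxon, chi-square and Fisher results as descriptive. Tabulate age and ART duration by arm among the women analysed at month 36. State one definition of the ART-duration match.

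**Cost.** A few sentences and a little more analysis. Age category, ART duration and CD4 count are already listed for both arms; age in years and CD4 at ART start would have to be taken from the records. The main result becomes model-based. Adjustment does not remove confounding by clinic or by enrolment in the parent study, since each coincides with arm; the report should say so.

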## Specific Objectives

**Primary objectives:**

- Determine the effectiveness of the *WHO Package of Essential Non-communicable Disease interventions for primary health care in low resource settings* (WHO PEN), integrated with standard of care HIV management guidelines, in identifying and in modifying risk factors for atherosclerotic cardiovascular disease in women receiving HIV care.
- Compare cardiovascular disease (CVD) risk scores using the WHO PEN *WHO/ISH Cardiovascular risk prediction chart for WHO epidemiological sub region AFR E*, *Data collection on adverse effects of anti-HIV drugs study (DAD risk assessment) and Framingham risk assessment* with short-term cardiovascular disease outcomes (presence of subclinical atherosclerosis by means of CMIT, presence of CVA, Myocardial infarction, Angina) in women aged over 40 years.

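### Continuous risk factors are compared between two non-randomised clinic cohorts with no stated use of entry values, so a pre-existing clinic difference could be reported as modification by the intervention

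*Protocol*

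**What the plan says.** All references are to the Protocol.

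- **Objective.** The first primary objective (Specific Objectives) is effectiveness "in identifying and in modifying risk factors for atherosclerotic cardiovascular disease in women receiving HIV care".
- **Design.** Overview, Study Design: "This study is a prospective two-arm, quasi-experimental design comparing a primary health care intervention plan with usual care". Under Sampling: "Method of selection will be via convenience sampling". The intervention arm comes from an observational cohort already followed at a research clinic. The control arm comes from a public primary-care clinic.
- **Safeguard against selection bias.** Measures to ensure validity: "careful matching between cohorts by age category and by duration of ART aims to counteract the potential for selection bias".
- **Test.** Statistical methods: "The continuous variables will be compared by use of t-tests or Wilcoxon rank sum tests". Logistic regression is described for predictors of cardiovascular disease and of carotid atherosclerosis. A separate line under possible confounders promises a multivariate regression (its key word is garbled) and lists no covariates. The same section expects the intervention arm to differ, with controlled study settings and possibly higher CD4 counts at ART start.
- **Control measurements.** Plan for Data collection: no study investigations at entry, chart review every 6 months, and one study measurement at year 3.
- **Schedule of evaluations** (columns: intervention, control charts before the final visit, control final visit): "BMI (6monthly) | BMI (6monthly) | BMI" and "Systolic BP (6monthly) | Systolic BP | Systolic BP". Fasting lipogram is also in the control chart column. Waist circumference, pulse, fasting glucose, hsCRP, urine microalbumin, smoking, diet, exercise and the three risk scores are blank there.

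**The concern.** Modification means change from where a woman started. A two-sample test of month-36 values measures where the two cohorts ended, which is the sum of any intervention effect and any difference already present at entry. Randomisation would make the entry difference zero on average. Here the arms are convenience samples from two different kinds of clinic, so there is no such guarantee, and the protocol itself anticipates differences. Unless entry values enter the analysis, the study could credit the intervention with a difference between clinics. For BMI and systolic BP, data that would help are already in the collection plan.

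**Working it through.** **Plan's own figure.** There is none for a continuous outcome: the protocol gives no standard deviation, correlation or detectable difference. Its sample size rests on metabolic syndrome, a binary outcome, and does not bear on this point. The figures below are illustrations on stated assumptions.

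**Inputs**
- Per arm: 200 ("400 HIV-infected women consisting of an intervention arm of 200 women co-enrolled in the PROMOTE study", with an equal control arm). Less the 10% loss allowed under Sampling: 200 × 0.9 = 180.
- Assumed: systolic BP standard deviation 15 mmHg; two-sided 5% test; no intervention effect; a between-clinic gap that persists unchanged to month 36; entry-to-final correlation r of 0.5 to 0.7 unless stated.

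**Step 1: unadjusted test at month 36**
- SE = 15 × √(2/180) = 1.58 mmHg.
- Rejection probability = Φ(gap/SE − 1.96) + Φ(−gap/SE − 1.96).

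| Persisting gap | gap/SE | Probability of a false effect |
|---|---|---|
| 2 mmHg | 1.26 | 24% |
| 3 mmHg | 1.90 | 48% |
| 5 mmHg | 3.16 | 89% |

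**Step 2: the same without choosing a standard deviation.** With 200 per arm, SE = √(2/200) = 0.1 SD. A persisting gap of 0.1, 0.2, 0.3 or 0.5 SD gives rejection in 17%, 52%, 85% or 99.9% of studies, against a nominal 5%. The 3 mmHg case above is 3/15 = 0.2 SD.

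**Step 3: two entry-based analyses under the same stable gap (200 per arm, 0.2 SD)**
- Change score: the gap cancels and the rate is 5%.
- ANCOVA on the entry value: a residual gap of b(1 − r) remains, with SE = √[2(1 − r²)/n × (1 + b²/4)]. At r = 0.8: 0.2 × 0.2 = 0.04 SD over 0.060 SD = 0.66, giving 10%. At r = 0.6 the rate is 17%.

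The two estimators differ in non-randomised arms, so the plan has to name one as main.

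**Step 4: precision relative to the unadjusted test**
- ANCOVA variance ratio 1 − r²: 0.75 at r = 0.5 and 0.51 at r = 0.7, a cut of 25% to 49%.
- Change-score variance ratio 2(1 − r): 1.0 and 0.6, a cut of 0% to 40%.

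**Step 5: what the change analysis brings in.** Control values switch from chart to study measurement at month 36, while the intervention arm is study-measured throughout. A systematic offset between the two sources passes directly into the difference in change. With r = 0.5 and 180 per arm, SE = 15 × √(2 × 0.5) × √(2/180) = 1.58 mmHg, so a 3 mmHg offset alone gives a false effect with probability 48%. Hence the chart-only sensitivity analysis under the fix.

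**The case against.** **The test family does not fix the quantity tested.** The statement names neither a time point nor level versus change, and a t-test on change would fit it. The analysis plan is not shown and could settle this. That stands in part. A reader might infer that the protocol commits to raw month-36 levels, but it does not say so. What it does is name unadjusted two-sample tests and mention no entry value anywhere in its analysis text.

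**Safeguards exist.** The cohorts are matched, and multivariate regression is promised. A reader might infer that confounding is ignored, or that the regression can only be logistic. The wording supports neither: the regression term is garbled, and the table of associations pairs age, ART regimen, ART duration and CD4 with BMI and systolic BP. Even so, matching covers only age and ART duration, and no line brings in the entry value of the outcome.

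**The powered outcome is binary.** The hypothesis speaks of more women, and the sample size uses metabolic syndrome. This is true. The fix below does not reach that outcome, because control waist circumference and glucose are absent before month 36. The point is confined to continuous risk factors, which the primary objective also covers.

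**Chart data may be thin.** The section on current CVD risk modification says vital signs are usually taken, but also that national guidelines recommend no BP or lipid screening in ART follow-up, and that lipids are analysed for women who need protease inhibitors. Completeness is unknown, and women with chart lipids may be selected by regimen. This stands, so it cannot be said how much bias would be removed.

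**Conclusion.** The point holds for continuous risk factors and should be corrected. The only between-arm method stated for them uses no entry value, in arms formed by clinic and convenience, and neither the matching nor the regression line supplies one. The false-effect probabilities of 24%, 48% and 89% rest on the assumed 15 mmHg standard deviation, 180 per arm and a gap that persists. They show sensitivity to a gap and are not evidence that one exists.

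Two further inferences go too far. Entry adjustment does not guarantee an unbiased result: difference in differences needs parallel trends, ANCOVA leaves part of a stable gap, and the chart-to-study switch is a new source of bias. Nor does the ANCOVA precision gain carry over to a change analysis, which gains nothing at r = 0.5.

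**What to change.** In Statistical methods, replace the unadjusted test as the main between-arm analysis of BMI and systolic BP, and of fasting lipids where charts hold them.

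1. **Main analysis:** difference in change from the first value near entry, from a mixed model with arm, time and arm-by-time, adjusted for age, ART duration, ART regimen and entry CD4. The schedule already lists these covariates in both arms.
2. **Sensitivity analysis:** ANCOVA on the entry value.
3. **Sensitivity analysis for the measurement switch:** only control chart readings up to the last chart review, compared with intervention values at the same time.
4. **Completeness:** report how many control women have an entry value for each factor.
5. **Factors with no control value before month 36** (waist circumference, pulse, glucose, hsCRP, microalbumin, smoking, diet, exercise, risk scores): report a covariate-adjusted month-36 difference and do not claim modification.

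The cost is analysis wording, plus extraction of chart values already planned, with no added visits or participants. The downside is dependence on chart readings that are noisier, partly missing and possibly offset from study measurements, and on the parallel-trends assumption, which should be stated.
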